# Data gathering:

## Quality management:

The study will be conducted in compliance with this protocol and the ICH-GCP in all sites. In each site, requirements of the Country health authority (Health Canada for Canadian sites) will be followed.

To ensure high quality data, all staff at all participating sites will receive initial training in the study protocol, procedures, and data requirements. This will include training in good clinical practice (GCP). Note that all sites participating in this trial have previously participated in randomized trials, notably our 4R vs 9INH trial, and have previously received GCP training. Hence for most this will be refresher training.

Study sites will also receive periodic monitoring visits during the conduct of the trial, to ensure that the study is conducted in accordance with protocol and to check for quality of data collected.

The principal investigator at coordinating site and the principal investigators at study sites, will be in charge of maintenance of the master binder with essential documents of the study, following GCP recommendations for the documents with participants’ confidential information.

During monitoring visits from the coordinating center, and if any visits occur for auditing, REB review and regulatory inspections, study site investigators will provide direct access to all essential documents including source data and documents.

Data management of collected data will be done during the study and before final analysis by the coordinating center. Queries will be sent to study sites to correct erroneous data or complete missing information. All data collected will be used in primary and secondary analysis.

## Pre-treatment:

Potential participants who may meet the eligibility criteria will be asked by the treating team, if they would like to meet research staff. Those who are not interested in participating will receive standard care from the treating team. For those who accept to meet with study team, their eligibility criteria will be checked and those who are eligible will be asked to provide informed consent. For those who consent a baseline evaluation will take place. In this baseline evaluation, all usual clinical and demographic information will be collected including indication for LTBI treatment (i.e. risk factors as being a close household contact, having immunosuppression, etc).

A close household contact (HHC) will be defined as persons who, over the past 3 months, slept in the same house at least one night per week, or spent at least 5 hours per week in the same house as a patient with newly microbiologically diagnosed active pulmonary TB (index TB patient). In sites in which DST or GeneXpert is done routinely for pulmonary TB patients, DST or GeneXpert results for rifampin for the index patient of each HHC will also be recorded.

Prior to enrolment all potential participants must have no symptoms suggestive of active TB, a chest x-ray (within a maximum of 6 months from the date of enrolment) that is considered to have no evidence of active TB, and a positive TST or IGRA as defined above. If the potential participants have abnormalities on chest X-ray, or TB symptoms, they will undergo investigation including sputum AFB smears/ TB cultures and/or GeneXpert. If these investigations to exclude active TB are negative, then they will be eligible for enrolment.

A pregnancy test will be performed prior to enrolment for all women of child bearing potential, unless the treating team judges it is not appropriate. For adolescents, results of pregnancy test will be disclosed to participants who are 14 years old or older and to participants and caregivers if less than 14 years old. Participants who are found to be pregnant will not be enrolled in the study, but an alternative individualized plan for LTBI management will be discussed with treating team and patients.

## During treatment

Patients will be seen by their primary health care providers after 2, 4 and 8 weeks of treatment for those randomized to **2R_20_**  or **2R_30_** and after 4, 8, and 16 weeks of treatment for those randomized to **4R_10_**. In this way the number, and approximate spacing of visits with their health care providers will be the same for all arms, to minimize any effect of visit frequency, and intensity of follow-up, on treatment completion. During these treatment phase visits, patients will be examined and questioned regarding symptoms of active TB as well as symptoms of adverse events. Participants will be asked to bring their medications with them at all visits. Pill counts will be done, and pills for the next treatment interval dispensed. The number of doses taken will be calculated at each visit. If sub-optimal adherence is noted (less than 80% of doses dispensed) the participant will be counselled by the usual treating team, following normal clinic procedures.

If a participant does not come on time for a scheduled treatment phase follow-up visit (is a no-show), they will be reminded – by the usual treating team and following usual procedures for non-study patients at the study site. Patients who decide to stop therapy – because of intolerance, or other reasons, will be encouraged to restart and complete therapy – by the usual treating team, and following normal procedures for non-study patients at the study site. If they maintain the decision to stop, then the study personnel will explain the need for post-treatment follow-up for two years. In our prior Phase 3 trial, while almost 30% of all patients stopped study treatment early, less than 5% were lost to follow-up. This was achieved through balancing the messages given to patients who were considering stopping therapy, or had sub-optimal adherence – emphasizing the desirability of completing study therapy, but also that they have the right to decide to stop taking therapy, or switch to alternative therapy, without any negative consequences to their care.

Routine blood tests for hemogram (hemoglobin, platelet counts, and leukocytes), and liver transaminases plus bilirubin will be drawn for all participants pre-treatment and after one month. For participants in the two high dose treatment arms, the same tests will also be done at the first follow-up visit after 2 weeks of treatment. For all participants additional tests can also be ordered at the discretion of the treating doctor. Creatinine and blood urea nitrogen will be tested after one month. The same protocol for lab testing will be followed in adults and children. Two blood draws (at 2 and 4 hours after drug intake) will be done after one month in all participants for population PK sub-study (see below). Information on rifampin drug levels will be collected for these patients in specific CRF.

If active TB is suspected then this will be investigated, managed and reported following a strict protocol. If active TB is diagnosed at another center then the study staff will travel to that center to obtain all relevant information including results for microbiological and radiologic and historic tests.

## Post-treatment

Patients will be contacted by telephone (or home visits if necessary) every 3 months after end of treatment until 26 months post-randomization. During these calls patients will be questioned regarding current symptoms of active TB, and any intercurrent diagnoses of active TB, or hospitalization for any reason. At the end of the follow-up period, home visits will be done for participants who could not be contacted by telephone or other means. If at any time active TB is suspected – then this will be investigated, managed and reported as specified above.

Every effort will be made to minimize loss to follow-up post-treatment.

## Pharmaco-kinetics (PK) studies

Two PK sub-studies will be conducted – an intensive study to determine the PK profile over many hours in a small group of participants at a single site, and a population PK – with limited sampling in a larger group of participants at all sites to assess determinants of variability in a diverse study population (age, sex, weight, ethnicity). Both PK sub-studies will be conducted after 4 weeks of therapy in all study arms, because we expect rifampin to reach steady state by this time. The population PK sampling will be performed at the same as the 4-weeks follow-up visit. The exact timing of the intensive PK sampling will be decided with the participants.

**Intensive PK sub-study**: This intensive sampling PK will be done in one of the study sites, in Bandung, Indonesia. Nine participants per arm in two age groups: 10-17, and 18 or older, will be recruited for the intensive PK sub-study (total 54 participants). On the PK sampling day, the participants will be asked to refrain from food at least 8h (4 h for children aged 10-17) before witnessed drug intake of a single dose of the study regimen at the clinic. They will remain fasting until 2 h after administration of the study drug. Serial venous blood samples will be collected just before, and at 1, 2, 4, 8, and 12 h after drug intake. Serial sampling will use an indwelling venous catheter (inserted with a standardised method) and a minimum of 1 cc of blood will be withdrawn at each sampling time. Blood samples will be immediately centrifuged and plasma will be stored at -80^0^C before bio-analysis using UPLC with a validated methods (Ruslami et al. 2007) at the pharmacokinetic lab of [name] (the site PI in Indonesia) in Bandung, Indonesia (Pharmacokinetic Laboratory, Faculty of Medicine Universitas Padjadjaran, Bandung, Indonesia.  [name],Indonesia). To obtain PK parameters of rifampicin, PK analysis will be done using standard noncompartmental methods in Phoenix WiNonLin version 6.3 (Ruslami et al. 2007).

**Population PK sub-study**: Samples for population PK sub-study will be collected in all participants. All samples collected for PK population sub-study can be utilized only for PK studies within this trial. Two blood samples (of 5 ml each) per subject will be taken 2h and 4 h after drug intake (van Beek et al. 2019). On the day of PK sampling, subjects will take their study drug at home with empty stomach. This will be self-administered and not supervised although they will be asked to record the exact time they took that day’s dose. At the clinic blood samples will be withdrawn using single sterile needle. Blood samples will be immediately centrifuged, plasma will be divided in 0.5ml aliquots and stored at -80^0^C. Frozen plasma samples from sites in Canada and Vietnam will be shipped (on dry ice) to the pharmacokinetic lab of [name] in Bandung, Indonesia, for the PK bioanalysis. All sampling process and bioanalysis afterward will be the same than for Intensive PK. To estimate the individual rifampicin exposure (AUC), PK analysis will be done with population PK approach (van Beek et al. 2019).

Information for the population PK will be contained in the consent for all participants at all study sites. Participants will have the option to agree to participate only in the main study – ie they can opt out of the population PK sub-study if they wish. Participants in the intensive PK sub-study at the Indonesia site will be asked to sign a separate consent for this sub-study.

## Enrolment and follow-up during COVID-19 related measures

During the COVID-19 pandemic, the following alternative procedures can be used for enrolment and follow up, although these alternate procedures must be approved by the local ethic committee, before being used. Site investigators will decide which procedure to use considering: the COVID-19 precautions in place at their site for health services delivery and the specific risks for each participant.

*Alternative enrolment procedures:* If the TB clinic operates so that LTBI treatment is started during a virtual (not-in-person) visit, enrolment can also be done virtually. The medical team that is recommending LTBI treatment will inform the potential participant of the study, and if the potential participant agrees, then the research team will contact them by phone. They will explain the study and read the consent form fully to the potential participant; if that person agrees, the same research staff person will sign the last page, attesting verbal agreement to participate in the trial.

*Alternative follow-up during treatment*: if TB clinic operates so that patients on LTBI treatment are followed virtually, then research follow-up visits can also be done virtually. Virtual visits are conducted by the treating team, and the research personnel will obtain the protocol required information from the treating team and may call participants if other, study specific, information are needed.

If any symptoms or other information is reported by the participant during a virtual follow-up visit that indicate the need for an in-person visit for a medical examination or lab tests this in-person visit will be scheduled as soon as possible.

Note: blood tests will be done following the planned schedule (i.e. pre-treatment, at 2 weeks and at 4 weeks after treatment starts for participants in high dose arms; pre-treatment and at 4 weeks for participants in standard dose arm).

*Data gathering during virtual visits*: data collected during virtual visits will be for most part the same that previously planned, as most information can be asked to the participants by phone or retrieved by the electronic participant’s chart (i.e. the laboratory results; radiology and microbiology results; participant’s weight).

The following two information will be collected differently during virtual visits:

- Medical exam at pre-treatment visit: if participant does neither report any respiratory nor any other symptoms, the research team will report the medical exam as “not done”.

- Count of remaining pills at each follow-up visit: during virtual visits the research team will ask the patient to report on remaining pills they have at home, so that the count will be “estimated” by participants instead of done in person by research team.

*Study drugs dispensing*: if follow-up is done virtually, dispensing of study drugs should happen at the same time as samples are drawn for blood tests. This means that the study medication would be given to the participants once they come at the clinic for the blood test (so that there are not extra in person visit for these participants), with attention to minimize the waiting time for the medications.

If study drugs must be dispensed at a different when the blood samples are drawn, or if the blood tests are done elsewhere than in the clinic, the study drugs can be delivered to the participants by courier.

During all in-person visits research personnel will comply with the procedures to minimize COVID-19 transmission risk that are in place at the clinic.

*Pharmacokinetic population study*: the blood sampling for the population PK component of the study will be done only if it is considered this will not cause any additional risk for COVID-19 transmission.

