# Outcomes

## Primary outcomes

The study has two primary outcomes: regimen completion and safety

Regimen completion: we have selected regimen completion as one of the two primary outcomes because we consider this to represent a summary measure of tolerability – i.e. the combined impact of patient decision to stop due to symptoms, such as stomach upset, anorexia, or fatigue, and health care provider decision to stop based on objectively measured events such as rash, or liver or hematological toxicity. This outcome has the additional advantages of being easy to define and measure, and does not require the added judgment of investigators, or an outside panel. Treatment completion is also readily comparable to completion measured in other studies.

This outcome will be based on the number of pills dispensed and pill counts during treatment phase follow-up visits. For the 2-month high-dose rifampin regimens, treatment phase medical follow-up visits by patients will be made two weeks after the start of therapy, at 4 weeks, and at end of therapy, and for 4R_10_ after 1 and 2 months and at end of therapy (total 3 follow-up medical visits for each regimen). Completion will be defined as taking 80% of doses within 120% of allowed time (48 doses within 72 days for the two-month regimens, and 96 doses within 144 days for the 4-month regimen).

Safety: Grade 3 to 5 adverse events (and Grade 1-2 rash) which result in permanent discontinuation of the study drug, and that are considered probably or possibly related to the study drug by the majority of a three-member independent and blinded Adverse Events panel. This panel (see below for details on panel) will review all events when the study investigator / primary health care provider stopped the study drug permanently because of their concerns of a potential drug-related adverse event. The panel will review these incidents blinded to rifampin dose, and independently from each other. Grading will be standardized using criteria established by the American Thoracic Society for hepato-toxicity (Saukkonen et al. 2006) and the National Cancer Institute for all other adverse events (National Cancer Institute Terminology Criteria for Adverse Events v4.0, at: <https://evs.nci.nih.gov/ftp1/CTCAE/CTCAE_4.03/Archive/CTCAE_4.0_2009-05-29_QuickReference_8.5x11.pdf>

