## Accountability procedures for investigational and comparator drugs:

For intervention arms (high dose arms) in Canadian site: the drugs for the two experimental arms, will be purchased as ROFACT 300mg (DIN 00343617), or RIFADIN 300mg (DIN [02092808](https://health-products.canada.ca/dpd-bdpp/info.do?lang=en&code=19034)). The capsules will be shipped with secure courier to the re-compounding pharmacy ([name], Pharmacie Frayne & associés, [name], [[contact]](https://www.google.com/search?client=firefox-b-d&channel=crow&q=[name]+pharmacy&spell=1&sa=X&ved=0ahUKEwiGpOCj9t7iAhXGV98KHfNyDIUQBQgtKAA&biw=1280&bih=608)) in Montreal. The blind, re-compounded capsules of 300mg and 450mg strength will then be shipped, also by secure courier, to the study site pharmacies in bottles. The labels for each bottle will specify if this contains the 300mg or the 450mg capsules. Each capsule (of 300mg and 450mg) will look the same, for blinding purposes and will not have anything written on it. At each site, for each participant randomized to the high dose arms, the pharmacist, or another health professional designated by the site qualified investigator, will be unblinded. This unblinded pharmacist (or health professional as above) will prepare a bottle with the number of doses needed for that participant until the next planned treatment phase follow-up visit. The bottle given to the participant will be labeled with their (participant’s) name, study ID, and a code corresponding to the arm to which participant has been randomized to. The code that identified each study arm will be known only to the pharmacist (or other designated health professional as above) at each site, designated to prepare the bottles for the participants. The code will also be known to the central study coordinator. This will ensure that the participant and his/her treating team will remain blinded.

At each visit, participants will bring their pill bottles, so that any remaining pills can be counted. Bottles will be refilled with doses needed until the next planned visit. The pharmacy at the site will keep a log of drug dispensed to participants, linking the content of the bottles prepared for each participant to the original bottle received from [name] pharmacy.

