## 1 Month isoniazid-rifapentine (1HP)

A short treatment of daily self-administered isoniazid and rifapentine taken for one month (1HP) has been recently tested in a phase 3 trial (Swindells et al. 2019). The multicenter trial, which enrolled 3000 adult participants with HIV, found that the regimen had equal efficacy and similar toxicity as daily self-administered 9-months INH. Completion, based on self-report at monthly visits by participants, was 90% in the 9INH arm compared to 97% in the 1HP arm. These rather remarkable rates of completion were accompanied by similar rates of efficacy and toxicity. The interesting findings of this study must be confirmed, in other trials in people living with HIV and also in non-HIV-infected adults and children.

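### Under virtual follow-up the pill count behind primary completion becomes the participant's own estimate, and no bottle count is requested even when the participant attends the clinic

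*Protocol*

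**What the plan says.** The protocol's Primary outcomes section fixes the data source: "This outcome will be based on the number of pills dispensed and pill counts during treatment phase follow-up visits". It sets the threshold there too: "Completion will be defined as taking 80% of doses within 120% of allowed time", that is 48 doses in 72 days or 96 doses in 144 days. The accountability section describes the routine: "At each visit, participants will bring their pill bottles, so that any remaining pills can be counted".

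The section on enrolment and follow-up during COVID-19 measures changes the routine for virtual visits. The participant reports the pills left at home, so that the count is estimated "by participants instead of done in person by research team". The same section keeps blood tests on schedule: weeks 2 and 4 on treatment in the high-dose arms, week 4 in the standard arm. For dispensing, it expects that "the study medication would be given to the participants once they come at the clinic for the blood test". There is an exception when blood is drawn elsewhere or at another time: "the study drugs can be delivered to the participants by courier".

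The section does not ask for the bottle to be brought or counted at the blood-test attendance. Nor does it ask for the count method to be recorded.

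**The concern.** Completion is one of two primary outcomes and the one that sets the sample size. An observed count gives a check on what the participant says; a number given by telephone gives none. For some participants the plan gives up that check on a day when staff could make it in person.

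Over-reporting turns true non-completers into recorded completers. The planning rates put 25% non-completers in 4R10 and 15% in each high-dose arm, so the same over-reporting rate adds more completers to the control arm. The difference then shrinks even if control participants report no less honestly than the others. The recorded outcome would also mix two instruments, with the mix depending on site and calendar period, and nothing in the section would let the analyst tell them apart.

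**Working it through.** **Inputs from the protocol** (Sample size considerations, Table 2 and its footnote): completion 75% v 85%, alpha 0.05, power 80%, ICC 0.33, 4 contacts per household, 65% household contacts, 412 per arm.

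**Reproducing the plan's figure**
- Two proportions, unpooled variance, two-sided 0.05: n = (1.960 + 0.842)² x (0.75 x 0.25 + 0.85 x 0.15) / 0.10² = 247.2. The plan states 247.
- Design effect for household contacts: 1 + (4 - 1) x 0.33 = 1.99, giving 492. The plan states 493.
- 65/35 mix: 247.2 x (0.65 x 1.99 + 0.35) = 406. The plan states 412, which is within 3%.
- 412 x 1.10 = 453 per arm; 453 x 3 = 1359, as stated.

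The power figures below use the plan's 412 per arm with the design effect it implies, 412 / 247.24 = 1.666. The effective n is therefore 247.24 per arm and the baseline power is 80.0%.

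**Assumptions not in the documents:** f, the share of participants followed virtually; m, the chance that a true non-completer among them is recorded as a completer because of self-estimation, taken as equal in all arms.

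**Effect on the difference**
- Recorded completion in an arm = p + (1 - p) x f x m.
- Control gains 0.25 x f x m; each high-dose arm gains 0.15 x f x m.
- Recorded difference = 0.10 - (0.25 - 0.15) x f x m = 0.10 x (1 - f x m).
- Power = Φ(difference / SE - 1.960), with SE = √[(p0(1 - p0) + p1(1 - p1)) / 247.24] at the recorded rates.

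| f | m | f x m | Recorded rates | Difference (points) | Power |
|---|---|---|---|---|---|
| 0 | any | 0 | 75.0% v 85.0% | 10.0 | 80.0% |
| 25% | 10% | 0.025 | 75.6% v 85.4% | 9.75 | 78.7% |
| 50% | 20% | 0.10 | 77.5% v 86.5% | 9.0 | 74.6% |
| 50% | 60% | 0.30 | 82.5% v 89.5% | 7.0 | 61.6% |

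Worked line for 9.0 points: SE = √[(0.775 x 0.225 + 0.865 x 0.135) / 247.24] = 0.0343; 0.09 / 0.0343 - 1.960 = 0.66; Φ = 0.746.

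**When the direction reverses.** Let m differ by arm. The difference is unchanged when 0.25 x m(control) = 0.15 x m(high dose), that is when over-reporting is 0.25 / 0.15 = 1.67 times as frequent in the high-dose arms. Above that ratio the difference grows. With f = 50%, m = 20% in high dose and 10% in control, it is 10.25 points and power is 84.0%.

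**The case against.** **The size is assumption.** Neither f nor m is in the documents, and the mild case costs little more than one point of power. The procedures are optional: they need local ethics approval, apply where the clinic already works virtually, and are chosen by site investigators. Only visits actually held virtually are affected. All of this stands.

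**Dispensing is an independent check.** Completion also uses pills dispensed, which the site pharmacy logs. With supply from visit to visit, a control participant who stops before the week-8 resupply has received about 56 doses and cannot reach 96, whatever is reported. A high-dose participant can hold the whole course from week 4. This limits the error to doses dispensed but not taken, and could make over-reporting easier in the high-dose arms. It narrows the concern without removing it.

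**Stronger readings that the documents do not support**
- A reader might infer that the control arm is more exposed, because 120 - 28 = 92 of 120 doses follow the week-4 blood test in 4R10, against 60 - 28 = 32 of 60 in the high-dose arms. But 4R10 also has a week-8 visit and resupply. If that supply is collected in person, 120 - 56 = 64 doses remain, and 64/120 = 53% = 32/60. The protocol does not fix how that resupply is made. A scenario with control over-reporting at twice the high-dose rate (40% v 20% at f = 50%, giving 6.5 points and about 49% power) therefore has no basis here.
- A reader might infer that the end-of-therapy count is always self-reported. That is so only when the visit is held virtually.
- A reader might cite the protocol's remark on another trial: "Completion, based on self-report at monthly visits by participants, was 90% in the 9INH arm compared to 97% in the 1HP arm". That trial enrolled adults with HIV on other regimens, so setting it beside the 78% for 4R in the earlier 4R trials shows nothing about self-report.

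**Equal over-reporting biases towards no difference.** It costs power and does not create a false superiority claim. This is true. The same shrinkage would, however, understate a real completion deficit in a high-dose arm.

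**The sensitivity analysis belongs in the SAP.** Agreed. But the collection rule is in the protocol, and no SAP can separate observed from estimated counts if the method was never recorded.

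**Conclusion.** The point holds as a modest, inexpensive improvement to a pandemic contingency. As written, the plan uses a less reliable measure for a primary outcome while staff could often make the better one on the same day. Given the planned 75% v 85% and equal over-reporting across arms, the recorded difference shrinks by 1 - f x m. Power at 412 per arm then runs from about 79% (f = 25%, m = 10%) through about 75% (50%, 20%) to about 62% (50%, 60%). Where the trial falls in that range cannot be settled from the protocol. The direction depends on over-reporting not being more than 1.67 times as frequent in the high-dose arms. No claim is made that the control arm is more affected.

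**What to change.** In the COVID-19 section of the protocol:

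1. Require participants on virtual follow-up to bring their bottle to any clinic attendance for blood tests or dispensing, for a staff count.
2. Where feasible, have the remaining capsules shown by video or photo at the end-of-therapy virtual visit. No blood test falls at week 8 or week 16, so step 1 does not reach that count.
3. Record at each visit whether the count was observed or self-estimated, so that a sensitivity analysis of completion by count method is possible.

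The cost is a wording change, one case report form field and slightly longer clinic attendances, which pulls against the section's aim of keeping waiting time short. Participants who are supplied by courier, have blood drawn elsewhere or cannot show their capsules stay self-reported, but would be identifiable.
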